### Study objectives

The objectives of this study are the following:To assess the acceptability of, and compliance with, the rehabilitation programme amongst patients, carers and clinicians and the fidelity of its delivery and to identify any adverse events.To assess the feasibility of a future definitive RCT by assessing the number of eligible patients, monitoring recruitment and retention rates, exploring the willingness of patient participants to be randomised and the willingness of patients and carers to complete process and outcome measures.To produce means and standard deviations of the quantitative measures so that effect sizes can be calculated for planning the future RCT.To explore how the intervention creates change in self-efficacy and fear of falling as potential mediators for improving function.To explore the methodological issues for conducting an economic evaluation alongside a future RCT including identifying the most efficient way of measuring patient level costs and health benefits, programme costs and potential payer stakeholders.To explore the feasibility and quality of data on service use extracted from patient electronic records compared with patient reported outcome measures. If successful, replacing patient reported outcomes of service use with data collection by researchers and the NHS information technology (IT) staff for electronic records has potential to reduce participant burden in future studies (this is referred to as the triangulation study later in the paper).

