### Randomised feasibility study

#### Selection of subjects for randomised feasibility study

Of all those admitted, we anticipate that we will be able to identify and invite 150 patients (50% of a conservative estimate of the total) from the three hospital sites across BCUHB during the 6-month study period to participate in the embedded feasibility study comparing usual care with the enhanced rehabilitation package using a randomised design. We will attempt to recruit 50 patients to this randomised feasibility study. The number of eligible patients, the recruitment and retention rates and the number who completed the outcome questionnaires will be recorded. It will be important to determine whether random allocation to either intervention arm is acceptable to patients, carers and clinicians providing the service. The feasibility study will also be an opportunity to test a package of process and outcome measures, including economic measures, for the main trial and to inform the effect size for a future sample size calculation. These patients will also be recruited to a triangulation study which aims to compare the quality of data collected about service use from patient-reported outcome measures compared with extracting the same information from patient electronic records.

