#### Randomisation

Patient participants who give their informed consent will complete baseline process and outcome measures before being individually randomised. The randomisation will be performed by dynamic allocation [21] to protect against subversion whilst ensuring that the trial maintains good balance to the allocation ratio of 1:1 both within each stratification variable and across the trial. Participants will be stratified by: (1) hospital and (2) gender.

Randomisation will be requested by the researcher who has taken informed consent and will be achieved by secure web access to the remote randomisation centre at the North Wales Organisation for Randomisation Trials in Health (NWORTH), Bangor University. This system will be set up, maintained and monitored independently of the trial statistician or other trial staff. The randomisation procedures will be aligned with NWORTH standard operating procedure 5.01 to ensure best practice. The key to the randomisation code will be held centrally by NWORTH.

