#### Patient completed measures - primary outcome

Barthel index [27].

This is a patient- or assessor-completed outcome measure of current functional status measuring individuals’ ability to care for themselves. It has evidence of validity when used in patients with musculoskeletal or neuromuscular disorders and is considered easy to use, reliable and sensitive to change. It focuses on the person’s level of independence on the following items: feeding, bathing, grooming, dressing, bowel function, bladder function, toilet use, transfers, mobility on level surfaces and stairs. It will be measured at baseline and at the 3-month follow-up assessment. The score range is 0 to 20 with lower scores indicating increased disability.

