An exploratory correlation analysis will be performed. Correlations will be calculated using Pearson’s product moment correlation coefficient for specific pairs of variables as outlined below. All of the correlations will be completed at both baseline and 3-month follow-up.Barthel index versus 8-ft get-up-and-go test.

This is exploring the relationship between the patient’s current functional status and the physical function test used to assess their agility and dynamic balance.Barthel index versus general self-efficacy scale/falls efficacy scale-international/self-efficacy for exercise scale.

There are three different self-efficacy measures that are being used within the feasibility stage of this study. All three of these will be correlated with the primary outcome measure to evaluate any differences between them and assist in the decision as to which measure to take forward to a full trial. The correlation is aiming to compare the patient’s self-efficacy with their current functional status to see if a link is present.

Preliminary exploratory analysis of the primary outcome measure (Barthel index) will be completed to find estimates of the means, standard deviations and confidence intervals for both of the treatment arms. These values will also allow the sample size calculation for the future RCT to be calculated. An exploration of any potential differences between the two groups in relation to the Barthel index will be completed using a *t*-test. The effect size and confidence intervals will also be calculated to inform a sample size calculation for a future definitive RCT. It is envisaged that a more complex analysis would be required to elicit an accurate description of the group differences; however, this would only be possible with a larger sample size.

The secondary outcome measures, which are the remaining outcomes at participant level, will follow the same procedure as for the primary outcome measure detailed above, as will the analysis for the only measure taken in relation to the carers (caregiver strain index). The results and appropriateness of the outcomes will be evaluated for continuation for a future RCT.

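### The Barthel comparison leaves out the baseline score and allocation factors although a simple adjusted model fits the sample, and the observed effect size is named as an input to the RCT sample size although the sample is justified only for the SD

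*Protocol article*

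**What the plan says.** Under Statistical analysis, the arms are to be explored on the primary outcome by a simple test: any "potential differences between the two groups in relation to the Barthel index will be completed using a" *t*-test. No covariate is named, and the text does not say whether the test is on the 3-month score or on change from baseline. Secondary outcomes and the carer measure follow the same procedure. The section accepts that a more complex analysis would describe the group differences better, but adds: "however, this would only be possible with a larger sample size".

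The data for an adjusted analysis are held. Of the Barthel index the article says: "It will be measured at baseline and at the 3-month follow-up assessment". Under Randomisation: "Participants will be stratified by: (1) hospital and (2) gender", with an "allocation ratio of 1:1".

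The effect size has a stated onward use: "The effect size and confidence intervals will also be calculated to inform a sample size calculation for a future definitive RCT". Study objectives gives the same purpose for the means and SDs: "so that effect sizes can be calculated for planning the future RCT". The section on selecting subjects for the feasibility study repeats it. The Sample size section, however, justifies 50 completers only as enough to estimate the Barthel SD.

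**The concern.** There are two separate issues.

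First, the stated reason for stopping at a *t*-test can be checked against the planned numbers. If baseline Barthel is prognostic, leaving it out widens the interval for the group difference. The plan also does not list the residual SD or the baseline to 3-month correlation, which an RCT analysed with baseline adjustment would need. The correlation pairs that it does list do not include Barthel at baseline against Barthel at 3 months.

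Second, a between-arm effect estimated from about 40 to 50 people is a very imprecise basis for the target difference of a definitive trial. The article states no important Barthel difference that could serve instead.

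**Working it through.** **Inputs from the article.** Recruitment aim: "We will attempt to recruit 50 patients to this randomised feasibility study". Allocation is 1:1, there are three hospitals, and the retention criterion is 75%. Sample size speaks of at least 50 completing. Both readings are carried: 50 × 0.75 = 37.5, about 38 completers (19 per arm), or 50 completers (25 per arm).

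**The plan's own figures.** The figure of 50 is a cited rule without inputs, so it cannot be re-derived. The retention bound can: 0.75 - 1.96 × √(0.75 × 0.25 / 50) = 0.63, which matches the stated 63% and confirms 50 as the randomised number.

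**Assumptions not in the article.** Baseline to 3-month correlation r of 0 to 0.7; standardised effect d = 0.3; RCT with 90% power at two-sided 5%.

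**Is the adjusted model estimable?** Its parameters are intercept, arm, baseline, two hospital terms and gender, six in all. Residual df are 38 - 6 = 32 or 50 - 6 = 44, against 36 or 48 for the *t*-test.

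**Precision of the group difference, in SD units.**
- *t*-test half-width: t(0.975, N - 2) × √(2/n), with n per arm. For N = 38: 2.028 × √(2/19) = 0.66.
- Adjusted half-width: t(0.975, N - 6) × √[(2/n)(1 - r²)(1 + 1/(N - 4))]. For N = 38 and r = 0.5: 2.037 × √(0.1053 × 0.75 × 1.029) = 0.58.

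| Analysis | 38 completers | 50 completers |
|---|---|---|
| *t*-test | 0.66 | 0.57 |
| Adjusted, r = 0 | 0.67 | 0.58 |
| Adjusted, r = 0.3 | 0.64 | 0.55 |
| Adjusted, r = 0.5 | 0.58 | 0.50 |
| Adjusted, r = 0.7 | 0.48 | 0.41 |

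**Bias.** In 4,000 simulated trials per setting with a true difference of 0.30, the mean *t*-test estimate lay between 0.291 and 0.305 and the mean adjusted estimate between 0.291 and 0.306. Neither is biased. Hospital and gender were given no effect on outcome, so the gain shown comes from baseline alone.

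**If the *t*-test were on change.** With equal SDs at both times (assumed), the variance factor is 2(1 - r): 1.4, 1.0 and 0.6 at r = 0.3, 0.5 and 0.7. The adjusted model has 1 - r²: 0.91, 0.75 and 0.51.

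**Precision of the observed effect.** SE(d) = √(2/n + d²/(2N)). At d = 0.3:
- N = 38: √(0.1053 + 0.0012) = 0.326; 95% CI -0.34 to 0.94.
- N = 50: √(0.0800 + 0.0009) = 0.284; 95% CI -0.26 to 0.86.

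**What this means for the RCT size.** Per arm, 2(1.96 + 1.2816)²/d² gives 234 at d = 0.3. At the upper limit it gives 24 (38 completers) or 29 (50 completers), and at the lower limit it is undefined. With the SD multiplied by √(1 - r²), 234 becomes 213, 176 or 120 at r = 0.3, 0.5 or 0.7.

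**The case against.** The strongest reply is that the analysis is labelled preliminary and exploratory, recruitment and retention are the main outcomes, and no efficacy conclusion rests on the test. That is right and limits the weight of the point. It does not remove it, because the output has a stated use in planning the RCT.

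The precision gain also depends on a correlation that the article does not give. Baseline is taken soon after surgery, and the article itself says that most other physical tests at that time would mainly reflect post-operative pain, so a low correlation is plausible. At r = 0.3 the gain with 38 completers is only 0.66 to 0.64 SD, and at r = 0 there is a small loss. This stands. So does the fact that adjustment does not cure the noise in the effect size, which comes mainly from the sample size: at r = 0.5 the half-width is still 0.50 to 0.58 SD.

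The baseline score may not be ignored altogether, since a change-score test is not ruled out. That is fair, but under equal SDs such a test is never more efficient than the adjusted model and is noisier than the raw comparison when r is below 0.5.

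Stronger readings are tempting, and the article does not support them:
- A reader might infer that the raw SD is the wrong input. The analysis of the future RCT is not stated, the raw SD is valid, and where baseline is prognostic it errs towards a larger trial.
- A reader might infer that the RCT could be abandoned because of a chance null result. The feasibility criteria under Statistical analysis and in the Discussion use eligibility, recruitment and retention only.
- A reader might infer that the RCT will be sized on the point estimate alone and so be underpowered. The article names the confidence intervals too, says only that they inform the calculation, and also plans to use the SD.

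**Conclusion.** The point holds in a limited form. The claim that anything beyond a *t*-test needs a larger sample is not correct for simple adjustment, which leaves 32 to 44 residual degrees of freedom. The cost of omitting it is precision, not bias. With 38 completers the half-width could fall from 0.66 to between 0.64 and 0.48 SD for assumed correlations of 0.3 to 0.7, with nothing gained if the correlation is near zero. The residual SD and correlation can still be computed from the data collected, so the gap is in planned reporting.

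The use of the observed effect is the weightier half. The sample was justified for the SD, and an estimate with a 95% half-width of about 0.57 to 0.66 SD cannot fix a target difference. Reporting its interval shows the uncertainty but does not say how a sample size follows from it. This is a worthwhile improvement to the planning output, not a flaw in the feasibility conclusions.

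**What to change.** For outcomes with a baseline measurement, replace the *t*-test by a linear model of the 3-month score on arm, baseline score, hospital and gender. Report the adjusted difference with its confidence interval, the residual SD and the baseline to follow-up correlation beside the raw means and SDs by arm. Remove or narrow the statement that a fuller analysis is possible only with a larger sample.

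State that the RCT target difference will be a prespecified important Barthel difference. Take the SD, the correlation and retention from this study, and use the observed effect and its interval only to check that they are compatible with that difference.

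This takes a few sentences and no new data. It costs four degrees of freedom relative to the *t*-test and the work of agreeing an important difference.

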#### Economic analysis

The enhanced rehabilitation programme will be fully costed using unit costs from a public sector multiagency perspective. Unit costs will be obtained from national sources of reference costs [41,42] and applied to information received from pilot questionnaires, namely salary band of therapists, time spent with the patient conducting rehabilitation, costs of travel and costs of any additional equipment. Costs of health and social care services used by the participants will also be costed using national sources of reference costs. The costs of service use and the cost of the intervention will be added together for use in a cost-effectiveness analysis.

The EQ-5D (3L) will be used to calculate QALYs over the 3-month study period, using area under the curve method [56,57]. An exploratory cost-utility analysis will be conducted to calculate a cost per QALY of the enhanced rehabilitation intervention. This cost per QALY generated will be compared to the NICE threshold range of £20,000 to £30,000 per QALY [58]. If a treatment/intervention costs more than £20,000 to £30,000 per QALY, then it would not be considered cost effective.

The ICEpop CAPability measure for Older people (ICECAP-O) [59] will be used to calculate a capability index score. An exploratory cost-effectiveness analysis will be conducted to calculate a cost per unit change in ICECAP-O score. We will compare the use of these two approaches, cost-utility analysis using QALYs and cost-effectiveness analysis using ICECAP-O, as a capability measure. We will explore the extent to which they can help guide commissioning decisions following a full trial and full economic evaluation.

The FEMuR feasibility study includes a discrete choice experiment [43,44] to look at the participant’s preferences for the ‘process’ of exercise programmes. The discrete choice experiment will assess which attributes are important to participants and will be administered at the 3-month follow-up. Based upon the data received from the feasibility study, we will assess whether the use of a discrete choice experiment is possible from a full scale RCT of the FEMuR multidisciplinary rehabilitation.

Finally, we will scope out the potential of conducting a social return on investment (SROI) analysis based on the data obtained from the feasibility study to inform whether a full SROI analysis is possible from a full-scale RCT of the FEMuR multidisciplinary rehabilitation intervention [60].

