#### Health economic measures

EuroQol EQ-5D (three levels) [37].

This is a patient-completed index of health-related quality of life, which gives a weight to different health states. It consists of five dimensions: mobility, self-care, usual activities, pain/discomfort, and anxiety/depression. Each has three possible responses. The responses record three levels of severity (no problems, some/moderate problems and extreme problems) which is then converted to a health utility weight using UK norms. It will be used at baseline and at the 3-month follow-up assessment and allows the calculation of quality-adjusted life years (QALYs), using area under the curve method which will be used as part of the economic analysis.ICEpop CAPability measure for Older people [38,39].

This is a patient-completed measure of capability in older people that focuses on well-being rather than health. It comprises five attributes: attachment (love and friendship); security (thinking about the future without concern); role (doing things that make you feel valued); enjoyment (enjoyment and pleasure); and control (independence). Each attribute has four possible responses. The responses record the extent of capability (all, a lot, a little, and none), and the five-digit outcome is converted to capability utility derived from UK norms. It will be used at baseline and at the 3-month follow-up assessment as part of the economic analysis.Client service receipt inventory (CSRI) [40].

The CSRI is a questionnaire for collecting retrospective information about study participants’ use of health and social care services, including voluntary services (e.g. charity services), including the components of the rehabilitation programme. This information will be combined with national sources of reference unit costs [41,42] in order to calculate health and social care service costs for the economic evaluation. It will be used at baseline and at the 3-month follow-up assessment as part of the economic analysis.Discrete choice experiment [43,44].

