#### Statistical analysis

The main outcomes of the feasibility study will be the descriptive statistics of recruitment and retention figures as follows:The number of patients screened for eligibility;The number of eligible patients and a comparison with the numbers in the cohort data set. A full trial will be considered feasible if 50% of the patients identified in the cohort study are eligible for inclusion in the trial. Using the lower end of a 95% confidence interval, this gives a minimum of 44% required to be eligible;Number of ineligible patients and frequency of predetermined reasons for ineligibility (lack of mental capacity to consent, not living independently, living outside the study area, age, did not have surgery for their hip fracture, living within the study area but outside the area where the intervention could be delivered, other);The number of eligible patients recruited (and so by implication were willing to be randomised) will be expressed as a percentage of the numbers in the cohort data set and as a percentage of the numbers identified as eligible in the feasibility study. The full trial will be considered feasible if the expected 25% of eligible patients are recruited to the trial, using the 95% confidence interval this gives a minimum of 18% recruitment;The number of eligible patients not recruited and the frequencies and reasons for this (e.g. burden, did not want to be in a research study);The number who withdraw after baseline assessment and randomisation and the reasons for withdrawal; andThe number who completed the various outcome measurements at baseline and at 3-month follow-up. The researchers who administer the outcome measures will record the reasons for any non-completion. The retention rate for the full trial to be feasible is 75%, again using a 95% confidence interval, this gives a minimum of 63% retention for the full RCT to be plausible.

The following demographics descriptors will be presented overall and per randomised group:Date of birth (age)GenderType of fractureMarital status and living arrangementsPlace of residence prior to admissionPlace of discharge from acute or community hospitalAbbreviated mental test score (AMTS)

All outcome measures will be presented descriptively at all of the time points that they have been collected.

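### No baseline-utility adjustment is specified for the two-point area-under-the-curve QALY, so the exploratory cost per QALY loses precision that collected data could restore at no cost

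*Protocol article*

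**What the plan says.** In the Protocol article, Economic analysis: "The EQ-5D (3L) will be used to calculate QALYs over the 3-month study period, using area under the curve method". Health economic measures and Table 1 place EQ-5D at two times only, baseline and 3 months. The QALYs then feed a ratio: "An exploratory cost-utility analysis will be conducted to calculate a cost per QALY of the enhanced rehabilitation intervention". The ratio is set against a decision range: "This cost per QALY generated will be compared to the NICE threshold range of £20,000 to £30,000 per QALY". The same section plans a parallel analysis with cost per unit of change in ICECAP-O, also measured at those two times, and a comparison of the two approaches.

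The Economic analysis section names no method for comparing QALYs between arms. The one between-group method in the article is under Statistical analysis: a t-test for the Barthel index, extended to all other patient-level outcomes, with anything more elaborate left to a bigger trial.

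On size and balance: "We will attempt to recruit 50 patients to this randomised feasibility study", allocated 1:1. "Participants will be stratified by: (1) hospital and (2) gender", so baseline utility is not balanced by design. The retention target is 75%.

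**The concern.** With only two measurements, half the weight in each patient's QALY falls on a utility recorded before randomisation, which the intervention cannot change. In a sample of this size the arms will differ at baseline by chance, and an unadjusted comparison carries that difference into the incremental QALY. The incremental QALY over 3 months is small, and it is the denominator of the cost per QALY, so modest noise moves the ratio a long way.

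Exploring methods for a later economic evaluation is one of the study objectives. What is at stake is how precise and interpretable that exploratory result is, and whether the comparison of the QALY and ICECAP-O approaches reflects the instruments or the way baseline was handled.

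**Working it through.** The article gives no QALY figure, so there is none to reproduce. The planning number of 50 can be confirmed from its retention limit: 0.75 − 1.96 × √(0.75 × 0.25/50) = 0.630, the stated 63%.

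**Inputs from the article.** T = 0.25 year; two EQ-5D points; 1:1 allocation of 50, so 25 per arm; 75% retained gives 0.75 × 25 = 18.75, about 19 per arm.

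**Assumptions, not in the article.** EQ-5D SD of 0.25 to 0.35; baseline to 3-month correlation ρ of 0.2 to 0.6; equal SDs at the two times.

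**1. Weight of baseline.** QALY = (T/2)(U0 + U3) = 0.125 × (U0 + U3). A baseline difference b between arms adds 0.125b directly. With equal SDs it adds a further 0.125ρb through its correlation with 3-month utility. The figures in step 2 count only the direct part.

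**2. Size of chance imbalance.** SE of the baseline difference = SD × √(2/n).
- SD 0.25, n = 25: 0.25 × √(2/25) = 0.071; × 0.125 = 0.0088 QALY.
- SD 0.35, n = 19: 0.35 × √(2/19) = 0.114; × 0.125 = 0.0142 QALY.

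So one standard error is about 0.009 to 0.014 QALY, or about £180 (0.0088 × £20,000) to £430 (0.0142 × £30,000) per patient. For scale, a true 3-month utility gain of 0.10 gives 0.125 × 0.10 = 0.0125 QALY.

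**3. Effect on the ratio (illustration, assuming an incremental cost of £200 and a gain of 0.10, direct part only).**
- b = 0: 200/0.0125 = £16,000 per QALY.
- b = −0.05: 200/[0.125 × (0.10 − 0.05)] = £32,000.
- b = +0.05: 200/[0.125 × (0.10 + 0.05)] = £10,667.

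**4. Gain from adjustment.**
- Unadjusted variance: 0.125² × SD² × 2(1 + ρ) × 2/n.
- Adjusted for U0: 0.125² × SD² × (1 − ρ²) × 2/n.
- Ratio: (1 − ρ²)/[2(1 + ρ)] = (1 − ρ)/2.

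| ρ | variance ratio | SE ratio | SE reduction |
|---|---|---|---|
| 0.2 | 0.40 | 0.63 | 37% |
| 0.6 | 0.20 | 0.45 | 55% |

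**5. Simulation.** 10,000 trials at each ρ, 25 per arm, SD 0.30, true gain 0.10:

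| ρ | SE unadjusted | SE adjusted | ratio | correlation with baseline imbalance, unadjusted | same, adjusted |
|---|---|---|---|---|---|
| 0.3 | 0.0170 | 0.0102 | 0.60 | 0.80 | 0.00 |
| 0.5 | 0.0184 | 0.0093 | 0.50 | 0.87 | 0.01 |
| 0.7 | 0.0195 | 0.0076 | 0.39 | 0.92 | −0.01 |

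Both estimators average 0.012 to 0.013, the true 0.0125, so neither is biased.

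**6. What remains after adjustment.** From the formula at SD 0.30 and 25 per arm, the adjusted SE is 0.0101, 0.0092 and 0.0076 for ρ of 0.3, 0.5 and 0.7. The 95% half-widths (× 1.96) are 0.020, 0.018 and 0.015, each wider than 0.0125.

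**7. ICECAP-O.** If the unit of change means 3 months minus baseline, a baseline difference b shifts that contrast by −(1 − ρ)b, while it shifts the QALY contrast by +0.125(1 + ρ)b. The two analyses would then be pushed in opposite directions by a similar imbalance. Replacing the change score by covariate adjustment multiplies its variance by (1 − ρ²)/[2(1 − ρ)] = (1 + ρ)/2: 0.60 at ρ = 0.2 and 0.80 at ρ = 0.6.

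**The case against.** The strongest objection is that the article does not say QALYs will be compared unadjusted. Area under the curve defines each patient's outcome and is compatible with later regression on baseline. The article is condensed, and covariates are often left to an analysis plan that is not at hand. The t-test text does not mention QALYs. All of this stands. A reader might infer that the plan commits to comparing raw areas, but the documents support only that no adjustment is specified and that the one stated between-group procedure is unadjusted, with more complex modelling put off. Anyone working from the article would reasonably do the unadjusted comparison, and one baseline covariate does not need a bigger trial.

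It can also be said that the consequence is limited. That stands too: the analysis is labelled exploratory, and progression rests on eligibility, recruitment and retention, not on cost per QALY. The comparison with the NICE range is nevertheless stated, so the precision of the ratio is not irrelevant.

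Finally, the size rests on an assumed SD and correlation, and the ratio (1 − ρ)/2 needs equal SDs shortly after surgery and at 3 months. Without that condition the ratio is (1 − ρ²)s3²/(s0² + s3² + 2ρs0s3), where s0 and s3 are the SDs at baseline and 3 months. This is still below 1 for any non-negative ρ, so the direction holds and only the amount changes.

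**Conclusion.** The point holds as a free improvement. As written, the plan leads to a less precise incremental QALY than the collected data allow. In a given trial, the unadjusted estimate moves with whatever baseline imbalance occurred: about 0.009 to 0.014 QALY per standard error of imbalance, given SD 0.25 to 0.35 and 19 to 25 per arm. Adjustment would cut the standard error by 37 to 55%, given equal SDs and ρ of 0.2 to 0.6.

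Three stronger readings are tempting and not supported:
- That the cost per QALY would be systematically biased. Randomisation makes the imbalance chance error.
- That having two time points causes the imbalance. It only fixes the weight of baseline at one half.
- That adjustment would settle the sign of the QALY difference or its side of the threshold. At about 50 patients the adjusted interval around a 0.0125 QALY gain still includes zero in the cases worked above.

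**What to change.** Add one sentence to Economic analysis: the incremental QALY will be estimated by linear regression of QALY on arm with baseline EQ-5D utility as a covariate (optionally also hospital and gender, the stratifiers), and that adjusted difference will be used in the cost per QALY. Treat ICECAP-O in the same way: estimate the arm difference at 3 months with the baseline score as covariate instead of using a raw change score, so that both approaches handle baseline alike when they are compared.

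The cost is a line of text and one model parameter per baseline covariate, which 38 to 50 patients can support. Table 1 already schedules both instruments at baseline, so there are no new data, no extra burden on participants and no change to the sample size.
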